## Abstract

**Background:**

Many people with multiple sclerosis experience problems with walking, which can make daily activities difficult and often leads to falls. Foot sensation plays an important role in keeping the body balanced whilst walking; however, people with multiple sclerosis often have poor sensation on the soles of their feet. Wearing a specially designed shoe insole, which enhances plantar sensory information, could help people with multiple sclerosis to walk better. This study will explore whether long-term wear of a textured insole can improve walking in people with multiple sclerosis.

**Methods:**

A prospective randomised controlled trial with two parallel groups will be conducted aiming to recruit 176 people with multiple sclerosis living in the community (Brisbane, Australia). Adults with a clinical diagnosis of multiple sclerosis, Disease Steps score 1–4, who are ambulant over 100 m and who meet specific inclusion criteria will be recruited. Participants will be randomised to a smooth control insole (n = 88) or textured insole (n = 88) group. The allocated insole will be worn for 12-weeks within participants’ own footwear, with self-report wear diaries and falls calendars being completed over this period. Blinded assessors will conduct two baseline assessments and one post-intervention assessment. Gait tasks will be completed barefoot, wearing standardised footwear only, and wearing standardised footwear with smooth and textured insoles. The primary outcome measure will be mediolateral base of support when walking over even and uneven surfaces. Secondary measures include spatiotemporal gait parameters (stride length, stride time variability, double-limb support time, velocity), gait kinematics (hip, knee, and ankle joint angles, toe clearance, trunk inclination, arm swing, mediolateral pelvis/head displacement), foot sensation (light touch-pressure, vibration, two-point discrimination) and proprioception (ankle joint position sense). Group allocation will be concealed and all analyses will be based on an intention-to-treat principle.

**Discussion:**

This study will explore the effects of wearing textured insoles over 12-weeks on gait, foot sensation and proprioception in people with multiple sclerosis. The study has the potential to identify a new, evidence-based footwear intervention which has the capacity to enhance mobility and independent living in people with multiple sclerosis.

**Trial registration:**

Australian New Zealand Clinical Trials Registry ACTRN12615000421538. Registered 4 May 2015.

## Background

Falls are a major threat to the health and well-being of people with multiple sclerosis (pwMS) [1, 2]. Up to 50 % of pwMS report falling within the past 6 months, and 50 % of these falls result in injuries [3]. Impaired mobility and balance are two major risk factors for falls in pwMS [2]. In one study, 85 % of pwMS reported gait disturbances as their main complaint [4] and continued loss of mobility amongst their greatest concerns for the future [5]. Impaired walking in pwMS is typically characterised by an increased mediolateral (ML) base of support, reduced stride length, step length and velocity, and prolonged double-limb support time during level ground walking, relative to healthy individuals [6–8]. Incipient signs of deteriorating walking ability can even be observed in the early stages of the disease [6–8]. Therefore, interventions that effectively preserve or enhance walking capacity are paramount to improving quality of life and maintaining independence.

Current rehabilitation strategies to improve gait and balance in pwMS predominantly involve exercise participation to address deficient motor function, with some consideration given to sensory training [9–13]. These multimodal approaches have been shown to significantly improve several clinical and functional measures in pwMS, including dynamic balance, rate of falls, physical activity levels, perceived balance confidence, walking ability and quality of life [9–13]. However, there is an urgent need to develop additional methods to complement exercise and which target MS sensory impairments [14–19] to a greater extent, in particular tactile sensation and proprioception, in order to preserve and enhance mobility for as long as possible. Previous evidence has shown that a strong relationship exists between foot sensation and standing balance performance in pwMS [15]. Similarly, a loss of lower limb proprioception, including joint position sense at the ankles and feet, in pwMS can detrimentally affect gait and standing balance, leading to greater dependence on compensatory motor mechanisms in order to remain upright [17, 19]. An increasing body of literature suggests footwear interventions may be another treatment option to help improve gait performance in pwMS [20–22].

Textured shoe insoles, designed to enhance plantar sensory information, have been shown to consistently alter gait patterns in the short-term, potentially improving walking stability in a range of clinical populations, including older fallers [23], adults with Parkinson’s disease [24] and pwMS [20, 21]. To date, exploratory studies indicate that textured insoles can lead to beneficial alterations in spatiotemporal gait parameters such as a reduced ML base of support [20], improved gait kinetics and kinematics [21] in pwMS. Significant increases in lower limb muscle activity during both stance and swing phases of gait, changes in knee and hip excursion and ground reaction forces, have been found immediately after pwMS wore textured insoles, with these changes attributed to enhanced stimulation of plantar mechanoreceptors [21]. Furthermore, after wearing textured insoles for 2 weeks, significant increases have also been observed in stride and step length, and significant decreases in the size of the ML base of support during level-ground walking – interpreted to represent a more confident gait pattern. These changes were observed independent of wearing the textured insoles, again supporting the theory that a sensory training effect may have occurred during the intervention period [20]. However, recent evidence reports no significant changes either in spatiotemporal gait measures during treadmill walking or plantar sensitivity after wearing textured insoles over a longer, 4-week intervention period in pwMS [25]. It is possible that any effects of textured insoles on gait may only be identified when walking in conditions that emulate everyday life [25]. Further, whilst no changes were observed in plantar sensitivity, alterations may have occurred in other measures of sensory function such as foot proprioception [25]. As such, the short-term effects of textured insoles on mobility, and their proposed underlying mechanisms in pwMS, remain unclear. It is possible that the benefits of textured insoles in pwMS may accrue, and that additional benefits may be observed, with prolonged wear over 4-weeks, but this has not yet been explored. Previous work has shown limited effects of textured insoles on gait and balance measures in pwMS immediately after wearing the insoles for the first time, with subsequent improvements observed following 2-weeks of wear [20].

This randomised controlled trial will determine whether wearing textured shoe insoles for 12-weeks can improve gait when walking over even and uneven surfaces in pwMS. The primary aim of this study is to explore whether prolonged wear of textured insoles alters ML base of support (as a measure of walking stability) from baseline assessment 2 to the post-intervention assessment. Secondary aims are to explore whether prolonged wear of textured insoles alters other spatiotemporal gait parameters including stride length, stride time variability, double-limb support time and gait velocity, gait kinematics (specifically lower limb joint and trunk movement), and changes in the perception of foot sensation or proprioception, as underlying mechanisms associated with improvements in spatiotemporal gait parameters.

## Methods

### Design

A prospective, parallel group, single blinded, randomised controlled trial with 176 pwMS living in the community will be conducted, conforming to the Consolidated Standards of Reporting Trials guidelines [26] (Fig. 1).

**Fig. 1 Fig1:**
[figure not shown]
Trial design

### Sample size

Sample size has been calculated for the primary outcome measure, ML base of support during even surface walking, based on our pilot data [20]. Our preliminary study reported mean (SD) readings at baseline for base of support of 13.78 (5.11) cm and a significant mean change of –1.66 cm (*P* = 0.02) at 2-weeks post intervention. With a power of 80 %, and alpha level of 0.05, a calculation for two related groups indicated that 76 participants were required in each group. In our pilot study, we recruited 46 pwMS, with no loss to follow-up across two visits (although completion of all test procedures was limited by fatigue in some participants). As this randomised controlled trial involves a longer intervention period, we will allow for a 15 % attrition rate. An 85 % retention rate over a 16-week period (baseline assessments at week 0 and week 4, intervention 12-weeks, post-intervention assessment at week 16) is appropriate based on previous MS intervention studies. Three randomised controlled trials with 12-week intervention periods conducted in pwMS, report retention rates of 82 % [27], 88 % [11], and 90 % [28]. Therefore, 88 participants per group will be recruited, giving a total of 176 participants.

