### Randomisation and blinding

The concealed randomisation schedule will be established using a computer-generated random number sequence, and maintained by an offsite investigator who is neither involved with the enrolment nor with assessment of participants. Consecutively numbered, randomly ordered, opaque envelopes containing group allocation (in a 1:1 ratio), will be opened consecutively after baseline assessment 2, by a second research assistant who is only responsible for administering the insoles. All investigators and the first research assistant, who are involved in the enrolment or assessment of participants over the duration of the trial, will remain blinded to group allocation. Following baseline assessment 2, the Principal Investigator and first research assistant will leave the gait laboratory to ensure blinding to the insole condition. The second research assistant will then fit the participant with their allocated insole, and provide advice regarding the frequency of wear, completion of insole wear diaries, and emergency contact details for local podiatry care. Participants will be instructed not to divulge their group allocation. As it is not possible for participants to be blinded to their allocated group (those in the intervention group will be able to perceive the textured material against the sole of their foot), the full aims of the study will be concealed. Participants will not be told that the intervention is designed to provide enhanced plantar sensory information which could potentially lead to changes in gait. Such knowledge could influence how participants walk and they could purposefully alter their walking patterns between conditions; debriefing will occur upon completion of the study. Furthermore, coding of participants will not refer to group.

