### Primary outcome measures

#### Spatiotemporal gait variables

The primary gait measure will be ML base of support when walking over an even and uneven surface. Our pilot study demonstrated that after 2-weeks wear of the textured insoles, the significant mean reduction in base of support was 1.7 cm (*P* = 0.02) compared to baseline measures [20]. The magnitude of this effect is highly clinically relevant as previous research indicates a mean difference of ~2 cm in base of support exists between pwMS and healthy controls [6, 7]. This suggests that the textured effect is clinically significant, and may be of sufficient magnitude to reduce base of support to a level similar to healthy adults.

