### Data analysis

All analyses will be conducted in a blinded manner, on an intention-to-treat basis, with the alpha set to 0.05. We will explore frequency distributions, percentages and calculate means and standard deviations for the outcome measures. Differences between intervention and control groups in spatiotemporal gait variables, gait kinematics, foot sensation or proprioception, over the intervention period, will be explored using General Linear Models (repeated measures analysis of variance, ANCOVA), in a two group (smooth control insole; textured insole) by three phase (baseline assessment 1, baseline assessment 2, post-intervention) model. We will adjust for potential confounding variables (e.g. age, sex, disease duration) by using these as covariates. Non-parametric tests will be used where data is not normally distributed or violates the assumption of sphericity. Multiple regression modelling will be used to determine any relationships between foot sensation, proprioception and measures of gait performance. Data will be analysed using SPSS version 22 (SPSS Inc., Chicago, IL 60606, USA).

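### The 80% power and 76 per group come from a paired calculation, but the trial compares two independent arms, so the 80% is not supported as written

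*Protocol article*

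**What the plan says.** The Sample size section says: "Sample size has been calculated for the primary outcome measure, ML base of support during even surface walking, based on our pilot data". It gives "mean (SD) readings at baseline for base of support of 13.78 (5.11) cm" and a pilot mean change of –1.66 cm (P = 0.02) after 2 weeks. With 80% power and alpha 0.05, "a calculation for two related groups indicated that 76 participants were required in each group". An allowance of 15% for attrition takes this to 88 per group, 176 in all.

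The design is different in kind. The Design section describes "A prospective, parallel group, single blinded, randomised controlled trial", and Randomisation and blinding has "opaque envelopes containing group allocation (in a 1:1 ratio". The Data analysis section examines "Differences between intervention and control groups in spatiotemporal gait variables" in a repeated measures/ANCOVA model with two groups and three phases. The end of the Background sets the primary aim as the alteration from baseline assessment 2 to post-intervention.

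The Sample size section states no between-group difference, SD of change, or correlation between baseline and follow-up.

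**The concern.** A paired calculation answers how many people, each measured twice, are needed to detect a mean change within one sample. Using its answer as a per-arm number ignores the sampling error of the second arm, which doubles the variance of the contrast.

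The inputs do not fit either design cleanly. A paired calculation needs the SD of the change, but the only SD given is the spread between people at baseline. The 1.66 cm is a change from the pilot participants' own baseline. It equals the between-group difference only if the smooth-insole arm does not change.

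What is at stake is how a null result would be read. If 80% is taken at face value, a non-significant difference looks like fair evidence against the insole. That reading is safe only if the power holds for the comparison actually made.

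**Working it through.** **Inputs.** From the Sample size section: SD 5.11 cm, difference 1.66 cm, alpha 0.05 (sidedness not stated; taken as two-sided), power 80%, 88 recruited per group, 15% loss. Completers: 88 × 0.85 = 74.8, about 75 per arm. (The 88 is 76 × 1.15 = 87.4 rounded up; 76/0.85 = 89.4 would give 90.)

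**1. Reproducing 76.** Paired formula: n = (SD × (1.96 + 0.842)/difference)² = (5.11 × 2.802/1.66)² = 74.4, so 75 by normal approximation. By noncentral t, power is 79.8% at n = 76 and 80.4% at n = 77. The stated 76 fits a two-sided paired calculation with SD 5.11. One-sided paired gives 59, and the unadjusted two-sample formula gives 149 (two-sided) or 118 (one-sided).

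**2. Same inputs, two independent arms, baseline not used.** n per arm = 2 × 74.4 = 148.8, so 149 (normal) or 150 (t). Power by noncentral t is 51.2% at 76 per arm and 50.7% at 75. The difference detectable with 80% power at 75 per arm is 2.35 cm. For scale, the primary outcome section says that "previous research indicates a mean difference of ~2 cm in base of support exists between pwMS and healthy controls".

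**3. Allowing for baseline.** Let r be the within-person correlation, assumed equal between all visits, with SD 5.11 at each visit. The SD that enters the two-sample test is:
- change from baseline 2: 5.11 × √(2(1 − r))
- ANCOVA on one baseline: 5.11 × √(1 − r²)
- ANCOVA on the mean of both baselines: 5.11 × √(1 − 2r²/(1 + r))

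Power for a difference of 1.66 cm at 75 per arm, with the 80%-detectable difference in brackets:

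| r (assumed) | Change from baseline 2 | ANCOVA, one baseline | ANCOVA, both baselines |
|---|---|---|---|
| 0.5 | 51% (2.35 cm) | 63% (2.04 cm) | 68% (1.92 cm) |
| 0.6 | 60% (2.10 cm) | 70% (1.88 cm) | 76% (1.75 cm) |
| 0.7 | 72% (1.82 cm) | 79% (1.68 cm) | 86% (1.53 cm) |
| 0.8 | 88% (1.49 cm) | 91% (1.41 cm) | 96% (1.26 cm) |

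**4. Can the pilot supply r?** Suppose P = 0.02 came from a paired t-test on n people. Then SD of change = 1.66 × √n / t, where t is the two-sided 2% point on n − 1 degrees of freedom, and r = 1 − (SD of change)²/(2 × 5.11²).
- n = 46: t = 2.412, SD of change 4.67, r about 0.58. Power is 58% (change), 68% (one baseline) and 74% (both baselines).
- n = 40: r about 0.64. Power with both baselines is about 80%.
- n = 30: r about 0.74. Power with both baselines is about 90%.
- n = 23: t = 2.508, SD of change 3.17, r about 0.81. Power is 89%, 92% and 96%.

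The article does not say how many people lie behind that P value, so the pilot leaves the question open.

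**The case against.** The strongest reply is that 51% belongs to an analysis that nobody plans. The primary aim is a change from baseline assessment 2, and the planned model includes both baselines. With a correlation of 0.7 or more, ANCOVA on one baseline gives 79% or better, and on both baselines 86% or better. The article also gives reasons why the correlation may be high. The walkway is cited as highly reliable. Both insoles were used in the pilot, and fatigue kept some pilot participants from completing all tests, so fewer than 46 people may lie behind P = 0.02. All of this stands, and it rules out presenting 51% as the trial's power.

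It is also true that 76 does not arise from the paired formula alone. Two-sample ANCOVA on one baseline at r = 0.7 gives 148.8 × (1 − 0.49) = 75.9, hence 76. But the article names a related-groups calculation and no correlation, so this cannot be taken as its stated basis. That 5.11 was the SD entered is likewise an inference, though the near-exact reproduction makes it likely.

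A reader might go further and infer that the trial is underpowered, that a null result would be close to a coin toss, or that 150 completers per arm are needed. The documents do not support this. Each statement holds only without baseline adjustment (or for a change score at r = 0.5), and the correlation is unknown.

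A separate analysis plan, if one exists, does not remove the point. The concern is with what the article states about its own sample size, not with something it leaves out.

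**Conclusion.** The point stands in this form: the sample size is justified by a paired, single-sample calculation while the trial compares two independent arms. The 80% is therefore unsupported for the comparison being made; it has not been shown to be unattainable.

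The unadjusted figure is about 51% at 75 completers per arm. Under an analysis that uses baseline, power lies between 51% and 96% over r = 0.5 to 0.8, depending on the correlation and on whether change, one baseline or both baselines are used.

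These figures rest on SD 5.11 cm at every visit, equal correlation between visits, two-sided testing, and a full 1.66 cm difference between arms. The last means no change at all in the smooth-insole arm. Any improvement there would lower every figure in the table, and the article gives no basis for its size.

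**What to change.** Keep 88 per group and rewrite the sample-size paragraph for the between-group contrast:
- Say that 76 is the number of pairs for a single-sample test, not a per-arm requirement.
- Replace the unconditional 80% with power and detectable difference for about 75 completers per arm, tabulated over r = 0.5 to 0.8 under the baseline-adjusted analysis. Name which form of that analysis the table refers to, since the group-by-three-phase model in the Data analysis section does not by itself settle it.
- State the assumption of no change in the smooth-insole arm.

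The correlation between baseline assessments 1 and 2, pooled and blinded, can update the table as data accrue. It will not be complete before randomisation, because each envelope is opened after that participant's own second baseline. It is also a 4-week correlation, whereas the outcome is measured 12 to 14 weeks after baseline assessment 2, so it may overstate the relevant one.

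The cost is one rewritten paragraph and no extra participants. The downside is that the stated power becomes conditional and possibly less favourable.

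### At the stated 85 % retention, 88 recruits per group leave about 75 completers, one short of the 76 the plan requires

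*Protocol article*

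**What the plan says.** The Sample size section of the protocol article works from pilot data: "mean (SD) readings at baseline for base of support of 13.78 (5.11) cm" and "a significant mean change of –1.66 cm". It sets the error rates, "With a power of 80 %, and alpha level of 0.05", and reports that "a calculation for two related groups indicated that 76 participants were required in each group". For losses it says "we will allow for a 15 % attrition rate". It then expresses the same allowance as 85 % retention over the 16 weeks from the first baseline visit to the post-intervention visit, and supports this with retention of 82 %, 88 % and 90 % in three earlier trials. It concludes: "Therefore, 88 participants per group will be recruited, giving a total of 176 participants". No inflation formula is printed.

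The Methods part of the Abstract uses the same number but attaches it to a different event: "Participants will be randomised to a smooth control insole (n = 88) or textured insole (n = 88) group". Under Randomisation and blinding, allocation envelopes are opened only after baseline assessment 2, which is at week 4.

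**The concern.** Retention is a proportion of the people who enter, and the section uses it that way when it cites other trials. The number to recruit is therefore the required number divided by the retention rate. The printed 88 is smaller than that quotient. As written, the recruitment target misses the section's own requirement when retention is exactly the planned 85 %. At stake is the internal consistency of a figure that carries the whole recruitment target, and a small part of the stated power.

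**Working it through.** **Inputs, all from Sample size:** 76 required per group; 15 % attrition, equal to 85 % retention; 88 recruited per group (176 in total); pilot change 1.66 cm; pilot baseline SD 5.11 cm; power 80 %; alpha 0.05. Sidedness is not stated; two-sided is assumed.

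**1. Reproduce the 76.** Treat the calculation as a paired t-test with the printed SD used as the SD of the differences. The standardised effect is 1.66 / 5.11 = 0.325. Solving for 80 % power gives n = 76.3 (74.4 by the normal approximation). The plan's 76 is reproduced, rounded to nearest.

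**2. Reproduce the 88.** Two common ways to inflate for 15 % loss are:

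| Formula | Result | Per group |
|---|---|---|
| 76 × (1 + 0.15) | 87.4 | 88 |
| 76 / (1 − 0.15) | 89.4 | 90 (89 if rounded to nearest) |

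Only the first gives 88. It applies the 15 % to the completers instead of to the recruits. Rounding cannot bring the second down to 88.

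**3. What 88 delivers.** 88 × 0.85 = 74.8, about 75 per group. For comparison, 90 × 0.85 = 76.5.

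**4. Break-even attrition.** 1 − 76 / 88 = 13.6 %. So 88 yields 76 completers only if attrition is no more than 13.6 %, and the plan allows for 15 %.

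**5. Effect on power, under the plan's own paired calculation.**

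| Completers per group | Power |
|---|---|
| 76 | 79.8 % |
| 75 | 79.3 % |
| 74.8 | 79.2 % |

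The loss is about half a percentage point.

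**6. Size of the gap in recruits.** 90 − 88 = 2 per group, or 180 − 176 = 4 in total, which is 4 / 176 = 2.3 % of the target.

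**The case against.** Three arguments can be made for leaving the figure alone.

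*The 88 may be the number randomised.* The 85 % covers 16 weeks, and allocation comes at week 4. If 88 per group are randomised, as the Abstract says, some of the loss has already happened. With losses spread evenly over time, retention over the last 12 weeks would be 0.85^0.75 = 88.5 %, and 88 × 0.885 is about 78, above 76. But even spacing is an assumption that the article does not make, and Sample size ties 88 to recruitment in the same paragraph that sets 16-week retention. What stands is that the article uses both words for one number and should say which it means.

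*The 15 % is a round allowance.* The three cited rates average 86.7 %, and 88 × 0.867 = 76.3. Individually they leave 72.2 (82 %), 77.4 (88 %) and 79.2 (90 %). This shows that uncertainty about retention is larger than the slip. It does not remove the slip, because the rate the plan adopts is 85 %, not the average.

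*It is immaterial.* On size this is largely right: half a point of power changes no decision in the trial. The printed figure is still wrong on its own premises, and correcting it costs almost nothing.

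A reader might also be tempted to go further and infer that removals for MS exacerbation (Participants section) come on top of the 15 %, so that the true shortfall is much larger. The article does not support that. It does not say whether the 15 % includes those removals, attrition up to week 16 could naturally include them, and it gives no exacerbation rate. Adding a further loss risks counting the same people twice.

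**Conclusion.** The error is real and minor. On the section's own figures, 88 per group leaves about 75 completers instead of 76, and the target that matches 85 % retention is 90 per group (180 in total). The cost is about one completer per group and about half a point of power. By itself it does not threaten the trial.

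The shortfall rests on one reading: that the 85 % applies to the 88, as the Sample size section presents it. It does not depend on how 88 was reached. Multiplication by 1.15 is the likely route because it gives exactly 88, but it is an inference.

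The power figures take the plan's paired calculation as given, with a two-sided test. They measure the effect of the slip on the plan's own terms and should not be read as the power of the comparison between textured and smooth insoles. Whether a formula for related groups suits a trial with two independent arms is a separate issue, and correcting the attrition step neither answers it nor endorses the 76.

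**What to change.** Keep 176 and amend the Sample size paragraph in three respects:

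1. State that 88 per group is expected to leave about 75 evaluable participants per group at 85 % retention, or equivalently that 88 covers attrition only up to 13.6 %.
2. Base the stated power on 75 per group (79.3 % under the present paired calculation).
3. Say whether 88 per group is the number enrolled at week 0 or the number randomised at week 4, and use the same word in the Abstract.

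This costs a sentence or two and no extra recruits. If the sponsor prefers to hold to 76 completers, the consistent target is 90 per group, four more participants in total. If the base number is recalculated for any other reason, the allowance should be applied by dividing by 0.85.
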